## Abstract

**Background:**

Patients with chronic kidney disease (CKD) are at high risk of developing heart failure and anemia, which is defined as type 4 cardiorenal-anemia syndrome (CRAS). CRAS aggravates the deterioration of both kidney and heart function, ultimately resulting in a high mortality. This study aims to examine the efficacy and safety of roxadustat in the treatment of type 4 CRAS.

**Methods and Design:**

This study is designed as a randomized, open-label, controlled trial. A total of 68 patients diagnosed with type 4 CRAS will be randomly divided into roxadustat group and erythropoietin with a 1:1 ratio. Participants in the roxadustat group will receive roxadustat with an initial dose of 70 or 100 mg three times a week, and participants in the erythropoietin group will receive subcutaneous injection of erythropoietin for 24 weeks, to maintain a hemoglobin ranging from 100 to 120 g per liter. The primary outcome is the change in heart function, including brain natriuretic peptide (BNP), 6-min walk test (6-WT), and left ventricular ejection fraction (LVEF). Secondary outcomes to be assessed include death, cardiovascular events, hospitalization regarding heart failure, Minnesota Heart Failure Quality of life scale (MLHFQ) score, New York Heart Association (NYHA) cardiac function grade, echocardiographic parameters including left ventricular diastolic diameter and volume (LVDD and LVDV) and ventricular mass (LVM), anemia related parameters, inflammatory parameters, and safety assessments.

**Conclusion:**

The findings of this study will provide potential evidence for roxadustat in CRAS management.

**Trial Registration:**

Chinese Clinical Trial Registry, ID: ChiCTR2100050031. Registered on 16 August 2021.

## Introduction

Type 4 cardiorenal-anemia syndrome (CRAS) is defined as a pathophysiological disorder whereby chronic kidney disease (CKD) leads to chronic cardiac dysfunction and anemia (1). The vicious circle between heart failure, anemia, and kidney disease contributes to a significantly worse prognosis and high mortality (2). Cardiovascular disease (CVD) is the leading cause of death in patients with estimated glomerular filtration rate (eGFR) <60 ml/min per 1.73m^2^ (3), while anemia is an independent risk factor for CVD in CKD patients. Compared with hemoglobin between 120 and 129 g/L group, the risk of heart failure in CKD patients with hemoglobin <100g/L increases by 1.99 times (4). For every 10g/L reduction of hemoglobin in dialysis patients, the risk of left ventricular dilatation increased by 42%, and the risk of new/recurrent heart failure increased by 18% (5). Despite the high prevalence and significance of renal anemia (RA), its management strategies are far from satisfactory. In China, only 39.8% of RA patients received erythropoiesis-stimulating agents (ESAs) treatment, 22.7% of patients initiated anemia-correction when hemoglobin decreased to less than 70 g/L, and only 8.2% of patients achieved a target hemoglobin of 110–120 g/L (6). Because of this, anemia-correction seems to be a reasonable approach to treat type 4 CRAS. ESAs together with iron supplements are conventional treatments for RA. Unfortunately, it was confirmed by the reduction of events by darbepoetin alfa in heart failure (RED-HF) study (7) that treatment with ESAs did not improve clinical outcomes in patients with systolic heart failure and mild-to-moderate anemia. On the contrary, the use of ESAs equivalent to more than 10,000 U/week of recombinant human erythropoietin (rHuEPO)/epoetin alfa will increase the risk of hypertension, stroke, thrombosis, thrombolysis in hemodialysis vascular access, and all-cause mortality (8). Iron overload due to excessive iron supplements also resulted in an increased risk of cardiovascular morbidity and mortality among hemodialysis patients (9). There is an urgent need to develop a safe and effective treatment for CRAS.

Roxadustat is a hypoxia-inducible factor-propyl hydroxylase inhibitor (HIF-PHI), developed as an agent for the treatment of RA (10). It can promote the production of endogenous EPO, increase the sensitivity of EPO receptor, diminish the level of hepcidin, and improve the iron homeostasis in CKD patients (11). Apart from its effectiveness in RA management, roxadustat displayed a lower risk of a composite cardiovascular endpoint including myocardial infarction, stroke, all-cause mortality, and unstable angina or congestive heart failure requiring hospitalization compared with epoetin alfa (12). Of note, this data is generally based on *post-hoc* analysis. Because of this, we designed a randomized controlled trial to assess the cardiovascular protective effects and safety of roxadustat in the treatment of type 4 CRAS.

## Methods and Analysis

### Study Design

This trial is an open-label randomized controlled study designed to address the efficacy and safety of roxadustat in patients with type 4 CRAS. The study is comprised of a 24 week treatment period and a 12 week follow-up period, with visits at 0, 4, 12, 24, 28, and 36 weeks. The trial flow is illustrated in Figure 1. The outcome measurements and time points of data collection are demonstrated in Table 1.

**Figure 1 F1:**
[figure not shown]
The flow chart of study design.

**Table 1 T1:** The schedule of enrollment, interventions, and assessments.

		**Study period**					
	**Enrollment**	**Allocation**	**Treatment**			**Follow-up**	
Time points (weeks)	−2	0	4	12	24	28	36
informed consent	√						
Eligibility screen	√						
Demographic data	√						
Medical history	√						
BNP		√	√	√	√		√
6-WT		√		√	√		√
LVEF		√		√	√		√
Death		√	√	√	√	√	√
CEs		√	√	√	√	√	√
MLHFQ scale		√		√	√		√
NYHA class		√	√	√	√	√	√
Echocardiography		√		√	√		√
Anemia parameters		√		√	√		
Inflammatory parameters		√		√	√		
Blood routine		√	√	√	√		
Urine routine		√	√	√	√		
Liver function		√	√	√	√		
electrocardiogram		√	√	√	√		
Adverse events		√	√	√	√	√	√

*BNP, brain natriuretic peptide; 6-WT, 6-min walk test; LEVF, left ventricular ejection fraction; CEs, cardiovascular events; MLHFQ, Minnesota Living with Heart Failure Questionnaire; NYHA, New York heart association. √, information collection, or parameter detection*.

### Participant Recruitment

Patients with CRAS as defined in the inclusion/exclusion criteria below will be invited to participate in the trial. Participants will be recruited from either the outpatient or inpatient of Beijing Hepingli hospital, Beijing, China. The recruitment was initiated in August 2021.

### Diagnostic Criteria

CKD and RA are defined by the Kidney Disease: Improving Global Outcomes (KDIGO) guideline (13), and chronic heart failure (CHF) is defined by the European Society of Cardiology (ESC) guideline (14). Type 4 CRAS is diagnosed in accordance with the Acute Dialysis Quality Initiative (ADQI) Consensus Conference (15).

### Inclusion Criteria

Age ≥18 years.Meets the diagnostic criteria of type 4 CRAS.New York Heart Association (NYHA) cardiac function grade II–IV, lasting for more than 4 weeks.Non-dialysis patients with CKD stage 3a-5.Hemoglobin level ≥ 70 and <100 g/L.Voluntarily signed the informed consent form.

### Exclusion Criteria

Severe cardiovascular and cerebrovascular events in the last 3 months including myocardial infarction, acute coronary syndrome, stroke, epilepsy, or thromboembolism (e.g., deep vein thrombosis or pulmonary embolism).Chronic inflammatory diseases that could impact erythropoiesis, such as systemic lupus erythematosus, rheumatoid arthritis, and abdominal diseases.Anemia due to ailments other than CKD, such as myelodysplastic syndrome, multiple myeloma, hereditary hematopathy, etc.Pregnant or lactating women.Severe liver insufficiency.Other serious systemic diseases.Allergic to components of agents used in the study.Mental disorder.

### Randomization, Blinding, and Allocation Concealment

The participants will be randomly allocated to the roxadustat group and erythropoietin group in a 1:1 ratio according to a computer-generated randomization sequence by a statistician who will be not involved in recruitment or data collection. This is an open-label study with investigators and participants unmasked to the information about allocation, while the statistician will be unaware of the treatment allocation. Any form of population-level summaries of outcome data will be prohibited before the end of the trial.

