### Outcome Measurement

Primary outcomes

The trial is designed to evaluate the improvement of heart function by roxadustat. Therefore, mean change in the brain natriuretic peptide (BNP), 6-min walk test (6-WT), and left ventricular ejection fraction (LVEF) estimated by echocardiography from baseline to 24 weeks will be applied as primary outcomes.

Secondary outcomes

(1) All-cause death and cardiovascular death.(2) Cardiovascular events including non-fatal acute myocardial infarction and non-fatal stroke.(3) Hospitalization regarding heart failure.(4) Change in Minnesota Living with Heart Failure Questionnaire (MLHFQ) score from baseline to 24 weeks.(5) Progress of cardiac function assessed by NYHA classification from baseline to 24 weeks.(6) Echocardiographic parameters including left ventricular diastolic diameter and volume (LVDD and LVDV) and ventricular mass (LVM).(7) Change in anemia-related parameters including the hemoglobin level, hemoglobin response rate (proportion of patients with hemoglobin elevation ≥ 10 g/L), serum iron, SF, TSAT, and hepcidin from baseline to 24 weeks.(8) Change in inflammatory parameters including high-sensitivity C-reactive protein (hs-CRP), procalcitonin (PCT), interleukin-6 (IL-6), tumor necrosis factor a (TNF-a), and lipoprotein a [Lp (a)] from baseline to 24 weeks.(9) Safety assessment consists of blood pressure, blood routine, urine routine, alanine aminotransferase (ALT), aspartate aminotransferase (AST), alkaline phosphatase (ALP), gamma-glutamyl transpeptidase (GGT), serum total bilirubin (TBIL), serum potassium, serum sodium, serum chlorine, and electrocardiogram.

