BNP and N-terminal pro-B-type natriuretic peptide (NT-proBNP) have been shown to be independent predictors of mortality (all-cause and cardiovascular) in advanced heart failure despite different cutpoints, time intervals, and prognostic models. In this study BNP is designed as one of the primary outcomes and is used as surrogate to calculate the study sample size, while NT-proBNP, with a relatively longer plasma half-life, is adopted as a surrogate in plenty of clinical trials. So, we think either BNP or NT-proBNP is acceptable as a prognostic marker of CHF.

As an open-label study, both the participants and investigators will be aware of the assignment and treatment. To ensure the quality of this study and minimize bias, the analysis of data will be performed by an independent statistician who is not involved in the study and blind to the allocation of treatment.

There are some limitations to this study. First, the study is single-centered and open-labeled, indicating there might be increased bias. Second, since most of the participants are unlikely to reach hard clinical endpoints, such as all-cause mortality or cardiovascular mortality, in the short study duration of 36 weeks, primary outcomes only include surrogate endpoints.

We expect that the results of this study will provide a scientific rationale for the use of roxadustat in improving the heart function of type 4 CRAS.

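### Analyst blinding is the plan's only stated answer to open-label bias, and it cannot remove bias that enters when LVEF, 6-min walk and NYHA class are measured

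*Protocol article*

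**What the plan says.** The protocol article's section on Randomization, Blinding, and Allocation Concealment sets out who is masked. On one side: "This is an open-label study with investigators and participants unmasked to the information about allocation". On the other, in the same sentence: "while the statistician will be unaware of the treatment allocation". No other masked role is named.

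The Discussion repeats that participants and investigators know the treatment, and then gives the remedy: "the analysis of data will be performed by an independent statistician who is not involved in the study and blind to the allocation of treatment". It presents this as the way to protect quality and limit bias. Among the limitations it concedes that "the study is single-centered and open-labeled, indicating there might be increased bias".

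The primary outcomes under Outcome Measurement are "mean change in the brain natriuretic peptide (BNP), 6-min walk test (6-WT), and left ventricular ejection fraction (LVEF) estimated by echocardiography", each taken from baseline to week 24. The secondary outcomes include left ventricular diameter, volume and mass by echocardiography, and "Progress of cardiac function assessed by NYHA classification from baseline to 24 weeks".

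The blinding section has two further safeguards. The randomization sequence comes from a statistician outside recruitment and data collection, and group-level outcome summaries are barred until the trial ends.

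**The concern.** The remedy does not match the problem. In an open-label trial, the bias to fear in a judgement-dependent outcome arises at the bedside or the echo workstation. LVEF depends on which frames are chosen and how borders are traced. Walking distance depends on encouragement and effort. NYHA class depends on how symptoms are elicited and graded. Once such a value is recorded, an analyst who does not know the arm labels reproduces whatever bias it contains.

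The arms are easy to tell apart (oral tablets against subcutaneous injections), the trial is at one centre, and the article describes the new drug as promising. An expectation in its favour is therefore plausible. The three primary outcomes are not ranked, and the Statistical Analysis section uses P < 0.05. A difference in LVEF or walking distance that came partly from assessment could thus be reported as an improvement in heart function even if BNP showed nothing.

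**Working it through.** **Step 1: match each outcome to the safeguards.** The plan gives no figure on this point, so the first check is to set its sections side by side.

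| Outcome (Outcome Measurement) | Where bias can enter | Stated safeguard acting there |
|---|---|---|
| BNP (primary) | Little; laboratory assay | Not needed to the same degree |
| LVEF (primary) | Image selection, tracing | None stated |
| 6-min walk (primary) | Coaching; participant's effort | None stated |
| LV diameter, volume, mass (secondary) | Image selection, tracing | None stated |
| NYHA class (secondary) | Grading; participant's symptom report | None stated |

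The independent sequence protects allocation. The bar on group summaries prevents accumulating results from influencing conduct. The blinded analyst protects analytical choices. None of the three acts on how an individual value is obtained.

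**Step 2: illustrate how sensitive the test is.** The documents give no SD for change in LVEF or walking distance and no estimate of assessor bias, so bias is expressed in SD units and varied.

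Inputs:
- n per arm = 27 (Sample Size Estimation, before dropout) and 34 (same section, after the dropout allowance).
- Two-sided 5% test (Statistical Analysis), critical value 1.96.
- No true treatment effect (assumption).
- Differential bias b = 0.1, 0.2 or 0.3 SD (assumption).

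Formulas (normal approximation):
- shift: δ = b × √(n/2)
- rejection rate = P(Z > 1.96 − δ) + P(Z < −1.96 − δ)

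For n = 27, √13.5 = 3.674. For n = 34, √17 = 4.123.

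| b (SD) | δ, n = 27 | Rate, n = 27 | δ, n = 34 | Rate, n = 34 |
|---|---|---|---|---|
| 0.1 | 0.367 | 6.6% | 0.412 | 7.0% |
| 0.2 | 0.735 | 11.4% | 0.825 | 13.1% |
| 0.3 | 1.102 | 19.7% | 1.237 | 23.6% |

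The nominal rate is 5%. A bias of 0.2 SD more than doubles it, and 0.3 SD raises it about four- to fivefold. These rates are the same whether or not the analyst is blinded.

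**The case against.** The strongest reply is that the point rests partly on silence. A reader might infer that unmasked staff read the echocardiograms and run the walk tests. The article does not say so: it unmasks investigators and participants, without saying that sonographers or walk-test staff are investigators or see the allocation. A journal article also condenses a fuller protocol, where reading procedures often sit. This limits the point but does not dispose of it. The article has a blinding section, lists who is masked, and puts forward analyst blinding as its answer to open-label bias. That reliance is stated, and it is misplaced whatever a fuller document adds.

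Second, the limitation is disclosed. It is, and the article deserves credit for that. Disclosure does not reduce the bias, however, and masked echo reading is possible in an open-label trial.

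Third, BNP, which sets the sample size, is largely spared and gives an objective, if imperfect, cross-check on the other two primary outcomes. This stands.

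Fourth, masked staff cannot remove bias from participants who know their treatment, try harder on the walk or report fewer symptoms. This also stands: the remedy is fuller for echocardiography than for the walk test or NYHA class.

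Finally, a reader might infer that the plan contradicts itself about the statistician, since the blinding section has a statistician generate the sequence and then calls the statistician unaware of allocation. The documents do not establish a contradiction. The Discussion's analyst is independent and outside the study, and can be read as a second person. It is an ambiguity.

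**Conclusion.** The point holds in a limited form. The plan relies on analyst blinding to contain open-label bias, and that cannot reach bias arising at measurement in two of the three primary outcomes, the echocardiographic secondary outcomes or NYHA class. No masked assessment is provided for any of them in the article.

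The documents do not show that assessors are in fact unmasked, nor that any bias exists. Its size cannot be estimated from them. The only defensible magnitude is the illustrative range: about 11–13% false positives at 0.2 SD and about 20–24% at 0.3 SD, assuming no true effect and 27 to 34 per arm. A reader might want a single error rate for a bias of so many LVEF points. That would need an SD of LVEF change, which the documents do not give, and the answer would move with whatever value was assumed.

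The matter should be put right but does not undermine the trial as a whole, because BNP is largely unaffected and the design limitation is acknowledged.

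**What to change.** In the blinding section, state that:

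1. Echocardiograms are stored under study ID and measured by the existing readers without arm or drug information. Those already recorded are re-measured the same way where feasible.
2. The 6-min walk follows a fixed script.
3. Where the existing rota allows, the walk test and NYHA grading are done by staff who do not dispense or titrate study drug.

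If any of this is already practice, saying so is enough. Amend the Discussion so that analyst blinding is not presented as the remedy for measurement bias, and note that bias from participants' own effort and symptom reports remains. As a minor clarification, say whether the statistician who generates the sequence and the blinded analyst are different people.

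**Cost.** Protocol wording, coded echo requests and minor logistics. Whether the rota can supply separate walk-test and NYHA staff is not known from the documents, hence the condition. Recruitment began in August 2021 (Participant Recruitment), so walk tests and NYHA grades already completed cannot be redone. A change now would mix two procedures for those outcomes, and its date should be recorded.

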### Intervention

Eligible participants will be randomly assigned in a 1:1 ratio to receive either roxadustat or erythropoietin for 24 weeks.

All participants will receive optimized treatments for heart failure and renal anemia based on the 2019 ESC (16) and 2012 KDIGO practice guidelines. The detailed treatments are listed as follows:

(1) Treatment of heart failure: All participants will be recommended to take angiotensin-converting enzyme inhibitors (ACEIs)/angiotensin receptor blockers (ARBs), beta blockers, aldosterone blockers, or angiotensin receptor-neprilysin inhibitor (ARNi) as basic treatment for HF. The individualized strategy regarding the types and dosages of drugs will be obtained by their physicians. In order to reduce the adverse events of hyperkalemia and deterioration of renal function, ACEIs/ARBs administration should be avoided in patients with CKD stage 5 (eGFR <15 mL/min/1.73 m^2^), and ARNi administration should be avoided in patients with CKD stage 4 or 5 (eGFR <30 mL/min/1.73 m^2^), especially for patients with a serum potassium > 5 mmol/L. When the patients' serum potassium levels reach as high as 5.5 mmol/L, ACEIs/ARBs or ARNi should be halted.(2) Iron deficiency treatment: All participants will receive 60 mg of oral elemental iron daily, with dose titration every 4 weeks to achieve a target transferrin saturation (TSAT) between 20 and 40%, as well as serum ferritin (SF) between 100 and 300 μg/L. The dose should be decreased if TSA > 50% or/and SF > 300 μg/L. If oral iron therapy is ineffective or intolerable after a 4-week treatment period, participants will be prescribed intravenous sucrose iron 100 mg/time, three times a week, and TSAT and SF will be evaluated again after a cumulative dosage of 1,000 mg.

Erythropoietin group

The erythropoietin (EPO) group will be treated with rHuEPO at an initial dose of 100–150 U/kg/week, divided into 2–3 subcutaneous injections, or 10,000 IU subcutaneously once weekly, with no restriction on the manufacturer of rHuEPO. The goal of initial EPO treatment is to increase hemoglobin by 10–20 g/L per month. The dose of rHuEPO can be increased by 60 U/kg/week, to maintain a target hemoglobin ranging from 100 to 120 g/L.

Roxadustat group

Participants randomized to roxadustat group will receive oral roxadustat (FibroGen, Co. Ltd, H20180024), with an initial dose of either 70 mg (body weight between 40 and 60 kg) or 100 mg (body weight ≥ 60 kg), 3 times a week. Based on the results of phase III clinical study of roxadustat in non-dialysis Chinese patients (17), the dose will be adjusted every 4 weeks following the rule displayed in Table 2, to maintain a hemoglobin level between 100 and 120 g/L.

**Table 2 T2:** Dose adjustments of roxadustat.

**Δhemoglobin over the past 4 weeks (g/L)**	**Hemoglobin level (g/L)**			
	** <100**	**100– <110**	**110– <120**	**≥120**
< –10	Increase	Increase	No change	Hold, then resume dosing when hemoglobin <110 g/L at a dose that is reduced by 1 dose steps
–10 to 10	Increase	No change	Decrease	
>10	Increase	Decrease	Decrease	

*Investigator will adjust the dose in dose steps of 50, 70, 100, 120, 150, and 400 mg. The dose can be changed 1 step at a time, and the maximum dose is 2.5 mg/kg. Δhemoglobin, change in hemoglobin*.

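### The potassium stop rule at 5.5 mmol/L leaves out aldosterone blockers, so in CKD stage 5 it has nothing left to stop; Table 1 also gives potassium no time point

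*Protocol article*

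**What the plan says.** **Drug list and limits (Protocol article, Intervention, item 1).** All participants are to be recommended ACEIs/ARBs, "beta blockers, aldosterone blockers, or angiotensin receptor-neprilysin inhibitor (ARNi) as basic treatment for HF". The choice and dose of drugs are left to the treating physicians. Limits follow, with their purpose stated: "In order to reduce the adverse events of hyperkalemia and deterioration of renal function". They are:

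- ACEIs/ARBs are to be avoided in stage 5 (eGFR below 15).
- ARNi is to be avoided in stages 4 and 5 (eGFR below 30), with the added remark "especially for patients with a serum potassium > 5 mmol/L".
- At the upper potassium threshold the rule is "serum potassium levels reach as high as 5.5 mmol/L, ACEIs/ARBs or ARNi should be halted".

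**Population (Inclusion Criteria).** Non-dialysis patients with CKD stage 3a to 5.

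**Outcome and schedule.** Secondary outcome (9) under Outcome Measurement names serum potassium, sodium and chlorine as safety assessments, as items separate from blood routine. Study Design says of the schedule: "The outcome measurements and time points of data collection are demonstrated in Table 1". Table 1 has laboratory safety rows for blood routine, urine routine and "Liver function", each at weeks 0, 4, 12 and 24, but none for electrolytes.

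**The concern.** A stop rule that names drug classes should cover every class on the recommended list that acts on the hazard in question. Here the hazard is hyperkalemia, and the rule leaves out one of the listed classes that raise potassium. The omission bears most on the patients with the least renal reserve, because the other limits have by then removed the classes that the rule does name.

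The rule also depends on a potassium value. If the published schedule does not say when potassium is measured, neither the trigger nor the listed safety outcome has a stated time point. The Statistical Analysis section plans a between-group comparison of change in laboratory parameters, and for electrolytes the article does not say between which visits that change is taken.

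What is at stake is participant safety and the completeness of the safety data, not the efficacy result.

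**Working it through.** There is no planned figure to reproduce. The check sets the drug list, the limits, the outcome list and the schedule side by side.

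**Step 1. What the 5.5 mmol/L rule can act on, by CKD stage.** Inputs: the recommended list, the two eGFR limits and the stop rule, all from Intervention item (1). That aldosterone blockers retain potassium is general pharmacology; the article does not state it.

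| CKD stage | ACEIs/ARBs | ARNi | Aldosterone blockers | What the rule can stop |
|---|---|---|---|---|
| 3a, 3b | open | open | open, no limit given | ACEI/ARB or ARNi |
| 4 | open | avoid | open, no limit given | ACEI/ARB |
| 5 | avoid | avoid | open, no limit given | nothing, if the avoidance advice is followed |

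Beta blockers appear in the list but are not the subject of any of these limits. In stage 5 the only potassium-retaining class still recommended is the one the rule does not mention. In stages 3 and 4 the rule does act, but says nothing about an aldosterone blocker taken alongside.

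**Step 2. Table 1 against the safety outcome list.**

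- Rows in Table 1: consent, eligibility, demographics, history, BNP, 6-WT, LVEF, death, cardiovascular events, MLHFQ, NYHA, echocardiography, anemia parameters, inflammatory parameters, blood routine, urine routine, liver function, electrocardiogram, adverse events. Total 19; rows naming potassium or electrolytes: 0.
- Items in secondary outcome (9): blood pressure, blood routine, urine routine, ALT, AST, ALP, GGT, TBIL, potassium, sodium, chlorine, electrocardiogram. Total 12.
- Items with a row: blood routine, urine routine, electrocardiogram, and five through liver function, so 3 + 5 = 8.
- Items without a row: 12 − 8 = 4, namely potassium, sodium, chlorine and blood pressure.

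The blood routine row cannot be read as covering electrolytes, because secondary outcome (9) lists them apart. The adverse events row records events; it does not schedule an assay.

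**Step 3. Cost of a scheduled row.** With 68 participants and four visits at which blood is already drawn (weeks 0, 4, 12, 24), the upper bound is 68 × 4 = 272 assays of each electrolyte, or 3 × 272 = 816 in all, before any dropout.

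**The case against.** **Background care sits under guidelines and physician judgement.** Heart failure treatment is to follow cited practice guidelines, and each physician chooses drugs and doses. A competent physician will act on an aldosterone blocker at 5.5 mmol/L whether or not the article says so. This stands as a mitigating point. It does not remove the gap: the authors wrote class-specific limits despite that discretion, and the limits are incomplete against their own stated aim.

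**The text does not tell anyone to continue the drug.** A reader might infer that a participant at 5.5 mmol/L is to stay on the aldosterone blocker. The article does not support that reading. The sentence is silent on the class; it neither directs continuation nor says that the named classes are the only ones to stop.

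**An outright stop is not the only reasonable action.** Stopping or reducing the dose may each be acceptable, and the cited guidelines are not at hand to settle it. This stands, and the fix allows either.

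**Table 1 is condensed.** Five liver analytes share one row, and blood pressure and heart failure hospitalization have no row either. A reader might infer that potassium goes unmonitored, or is left for long stretches. If potassium were drawn only with blood routine, the later intervals would be 12 − 4 = 8 and 24 − 12 = 12 weeks. But the article does not say that it is drawn only then, its measurement is planned as a safety outcome, and the full protocol may give the visits. What remains is a mismatch within the article: Study Design presents Table 1 as the schedule, and a named outcome is not in it.

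**Adverse events are recorded at every visit.** Hyperkalemia that is recognised clinically would be captured. That is true, but it does not give the rule's trigger a measurement time.

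**Conclusion.** The point holds, and its main part is the stop rule. As written, the limits meant to reduce hyperkalemia leave one recommended potassium-retaining class with no potassium limit, no eGFR limit and no stop rule, and in stage 5 the 5.5 mmol/L rule has nothing to act on. The stage 5 conclusion assumes that the advice to avoid ACEIs/ARBs and ARNi is followed; where it is not, the rule still acts on those drugs.

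The missing electrolyte row (0 of 19 rows; 3 of the 4 unscheduled safety items) is a minor accompanying correction.

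The size of any harm cannot be estimated, since the article gives neither the share of participants on aldosterone blockers nor a hyperkalemia rate. The rule applies alike in both arms, and the sample size and the planned analysis of BNP, 6-WT and LVEF are unaffected. The correction should be made because it concerns safety in a vulnerable population and costs very little. The documents do not make a case for additional creatinine/eGFR assays or for potassium checks at weeks 8, 16 and 20; those go beyond the gap shown here.

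**What to change.** 1. **Extend the stop sentence in Intervention item (1)**, for example: *At a serum potassium of 5.5 mmol/L or above, stop the ACEI/ARB or ARNi, and stop or reduce the dose of any aldosterone blocker.* This costs one edited sentence. The downside is somewhat less aldosterone-blocker exposure, in both arms.
2. **Add a row to Table 1** for serum potassium, sodium and chlorine at weeks 0, 4, 12 and 24. Blood is already drawn at these visits, so the cost is one table row and at most the 272 assays per electrolyte worked out above. If the full protocol already schedules them, only the table needs to change.

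Neither change needs more patients, more visits or any alteration to the primary analysis.
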